### Sample size

Some researchers recommend that the sample size for each endpoint should be calculated separately, and the largest sample size should be chosen as the overall trial's sample size [30]. The study is designed with two primary outcome measures: cost and time. By calculation, the sample size calculated based on cost is larger. Therefore, it is selected as the total sample size. The type I error α is set at 0.05 (2-tailed analysis), and the test efficacy 1 − *β* at 0.9. Based on the combined standard deviation of 3987 in previously published literature [31], we estimate that the difference in cost between the two groups within 12 weeks after surgery is approximately 2000 RMB. Using the formula $$n = \frac{{2\left( {z_{\alpha } + z_{\beta } } \right)^{2} *\sigma^{2} }}{{\delta^{2} }}$$, we determined that 80 patients are needed in each group. Accounting for a dropout and loss to follow-up rate of 20–25%, we need to recruit a total of 200 patients.

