Wearable micro-sensing devices have become commonplace in the sports industry for real-time performance analysis of athletes [23, 24]. For instance, in the case of total hip arthroplasty and cardiovascular risk factors, accelerometry can be employed to monitor physical activity levels and estimate calories and energy expenditure by tracking movement patterns, including steps taken and distance traveled [25–27]. However, their potential use in healthcare has yet to be fully realized [28]. The number of studies on wearable motion sensors has grown in recent years, with many focused on knee replacements, providing additional information to clinical metrics [29]. This study aims to evaluate the cost, time savings and effectiveness of an innovative treatment approach using a new, simple monitoring device in conjunction with a mobile phone app to guide patient rehabilitation exercise. We hypothesize that patients in the experimental group would exhibit improved short-term functional outcomes and experience cost and time savings compared to patients in the control group.

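### Taking the larger of two unadjusted single-outcome sample sizes makes the stated 90% a per-outcome power at best: it is not secured for winning on both cost and time, nor for cost at a multiplicity-adjusted alpha

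*Protocol article*

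**What the plan says.** The Sample size section of the protocol article says that "The study is designed with two primary outcome measures: cost and time". It follows advice that "the sample size for each endpoint should be calculated separately, and the largest sample size should be chosen", and reports: "By calculation, the sample size calculated based on cost is larger". The error rate is two-sided 0.05, with no division between the two outcomes, and the power is given as "the test efficacy 1 − *β* at 0.9". The inputs for cost are an SD of 3987 from published literature and a difference of about 2000 RMB. The result is 80 per group, raised to 200 in total for 20 to 25% loss. The SD, difference and sample size for time are not given.

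The Background hypothesis is that experimental patients will have better short-term function and will "experience cost and time savings compared to patients in the control group". Data analysis says that multiple testing inflates the type I error and adopts a Bonferroni threshold of 0.002.

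**The concern.** Choosing the larger of two single-outcome sample sizes guarantees that each outcome, taken alone, reaches its target power. It does not guarantee that power for the trial as a whole. If a positive trial needs both outcomes, the chance of winning both cannot exceed the chance of winning on the weaker one. If either outcome is enough, testing both at 0.05 leaves the overall false-positive rate above 0.05, and correcting for that lowers the power for each outcome.

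The article fixes alpha, power and sample size, so this is a matter of what the stated figures deliver, not of detail left for later. A reader who takes 0.9 as the trial's chance of detecting the hypothesised savings would be misled. The same text also does not settle whether a win on cost alone makes the trial positive.

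**Working it through.** **Inputs.** From Sample size: SD 3987, difference 2000, 80 per group, two-sided 0.05, power 0.9. From Data analysis: threshold 0.002. Not in the document, so assumed: the standardised effect for time, set at 1, 1.2 or 1.5 times that for cost, and the correlation r between the two test statistics, 0 to 0.8. Ratios below 1 are left out because the article says cost needs the larger sample.

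**1. The plan's own figure.** n = 2(z_α + z_β)²σ²/δ² = 2(1.960 + 1.282)² × 3987²/2000² = 83.5, so 84 per group. The one-sided version gives 69. Neither reproduces 80.

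**2. Cost alone at 80 per group.** The standard error is 3987 × √(2/80) = 630.4, and 2000/630.4 = 3.173. Power at 0.05 is Φ(3.173 − 1.960) = 0.887 (0.884 using the t distribution). At 84 per group it is 0.902.

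**3. Both required, 0.05 each, 80 per group.** Power for time is Φ(ratio × 3.173 − 1.960). Joint power is the bivariate normal probability that both statistics exceed 1.960.

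| Effect for time ÷ effect for cost | Power, time | Both, r = 0 | Both, r = 0.5 | Both, r = 0.8 |
|---|---|---|---|---|
| 1.0 | 0.887 | 0.787 | 0.813 | 0.840 |
| 1.2 | 0.968 | 0.859 | 0.870 | 0.881 |
| 1.5 | 0.997 | 0.885 | 0.886 | 0.887 |

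No assumption about time can lift these above 0.887. At 84 per group the equal-effect row becomes 0.813, 0.835 and 0.858, and the 1.5 row about 0.90.

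**4. Either sufficient.** Power for at least one is the sum of the two powers minus the joint power. With equal effects at 80 per group:

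| Alpha for each | Cost alone | At least one, r = 0 | r = 0.5 | r = 0.8 |
|---|---|---|---|---|
| 0.05 | 0.887 | 0.987 | 0.962 | 0.935 |
| 0.025 | 0.824 | 0.969 | 0.928 | 0.889 |

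At 0.05 each, family-wise error with independent outcomes is 1 − 0.95² = 0.0975. At 0.025 each, 90% power for cost alone needs 2(2.241 + 1.282)² × 3987²/2000² = 98.6, so 99 per group.

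**5. The threshold in Data analysis.** 0.002 equals 0.05/25. If it covers the primaries, power for cost at 80 per group is Φ(3.173 − 3.090) = 0.533, and 90% would need 152 per group. With equal effects, power for both is 0.284 (r = 0) to 0.431 (r = 0.8).

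**The case against.** The best defence is that the section claims no joint power. It says openly that sizes were calculated separately, and 0.05 and 0.9 enter a single-outcome formula. That is fair, and it is why 0.9 has to be read as a per-outcome figure. The Background sentence is a general hypothesis that also names function, so it does not establish that both outcomes must succeed. A success rule could also sit in an analysis plan that is not shown. None of this rescues 0.9 for both outcomes or for cost at an adjusted alpha.

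Two stronger readings are tempting and should be resisted. A reader might infer that 90% also fails when either outcome suffices. The document does not support that: at unadjusted 0.05, power for at least one is never below that for cost alone and is about 94 to 99% with equal effects. The fault there is type I error. Even at 0.025 each it is 89 to 97%; the 82.4% and the 99 per group concern cost alone.

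A reader might also infer that the 10% risk of missing an effect is roughly doubled. That needs time to be powered no better than cost, which is the worst case under the article's own statement that cost needs the larger sample.

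Part of the shortfall comes from 80 in place of 84 and would exist with one primary outcome. If all 100 recruited per group were fully observed, power for cost at 0.05 would be 94%. But the plan expects losses and bases its power on 80.

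**Conclusion.** The point holds in limited form. The stated 90% is a per-outcome figure at unadjusted 0.05, and even for cost it is 88.7% at 80 per group. For both outcomes the ceiling is 88.7%. The shortfall against 90% runs from about 1 point to about 11, depending on the power for time and the correlation, neither of which is documented. For either outcome at 0.05 the exposure is a family-wise error of up to 9.75% under independence, not lost power.

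The largest gap arises if the 0.002 threshold governs the primaries: sizing at 0.05 then leaves cost with 53% power. The article does not limit that threshold to the secondary outcomes, so the two sections need to be reconciled. All figures rest on the stated SD and difference for cost and on normal approximations.

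**What to change.** In Sample size, state whether success needs both outcomes or either, and the alpha at which the primaries are tested. In Data analysis, say whether 0.002 covers the primaries, so that the two sections agree. Give the inputs for time, so that the range for both outcomes can be narrowed.

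Then replace 0.9 with the power at 80 per group for the chosen rule:

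- cost alone at 0.05: about 0.89
- both at 0.05 each: 0.79 to 0.89, with the assumption about time stated
- cost under a two-way split of alpha: at least 0.82
- cost if 0.002 applies: 0.53

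The cost is a change of wording and a less favourable stated power. No extra patients are needed.

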### Randomization and blinding

The 200 recruited patients are randomly assigned in a 1:1 ratio to either the experimental or control group using a computerized random number generator. Each patient is assigned a random number. Blinding is not possible due to the nature of the study, so neither patients nor physicians will be blinded to their group assignment. However, data analysts will not have access to any patient information other than their assigned number and will remain blinded during the statistical analysis of the collected data and presentation of results.

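### The sample-size formula gives 84 per group, not 80, and 200 recruits cover only the 20% end of the planned 20–25% loss, so power falls below the stated 90%

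*Protocol article*

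**What the plan says.** The Sample size section of the protocol article names two primary outcomes, cost and time. It says cost needs the larger sample and so sets the size of the trial. The inputs are all printed:

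- Error rate: "The type I error α is set at 0.05 (2-tailed analysis".
- Power: "the test efficacy 1 − *β* at 0.9".
- Spread: "Based on the combined standard deviation of 3987 in previously published literature".
- Effect: "we estimate that the difference in cost between the two groups within 12 weeks after surgery is approximately 2000 RMB".

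The formula shown is the standard one for two means, n = 2(z_α + z_β)²σ²/δ². The result is given as "we determined that 80 patients are needed in each group". The section then allows for losses: "Accounting for a dropout and loss to follow-up rate of 20–25%, we need to recruit a total of 200 patients". The Randomization and blinding section confirms the split: "The 200 recruited patients are randomly assigned in a 1:1 ratio", which is 100 per group.

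**The concern.** A reader who puts the printed inputs into the printed formula does not get 80. Separately, a single total of 200 is said to allow for a range of losses from 20% to 25%, yet it fits only the lower end, and only if 80 is accepted. The two slips act in the same direction: each makes the trial smaller than its stated assumptions require.

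The number per group, the recruitment total and the power should follow from one another, and here they do not. Power of 90% is claimed for a trial that, on its own planning assumptions, ends with 75 to 80 patients per group rather than 84.

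**Working it through.** **Inputs** (all from Sample size, except the allocation ratio, from Randomization and blinding): two-sided α = 0.05, so z = 1.95996; power 0.9, so z_β = 1.28155; σ = 3987; δ = 2000; stated n = 80 per group; stated loss 20–25%; 200 recruits allocated 1:1.

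**Step 1: attempt to reproduce 80 per group.**

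n = 2 × (1.95996 + 1.28155)² × 3987² / 2000² = 83.51, so 84 per group.

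Other readings do not give 80 either:

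| Reading | n before rounding up | n per group |
|---|---|---|
| Two-sided 0.05, power 0.9 | 83.51 | 84 |
| Same, rounded quantiles 1.96 + 1.28 | 83.44 | 84 |
| Same, σ/δ rounded to 2 | 83.98 | 84 |
| Same, by t-test | 84.49 | 85 |
| One-sided 0.05 (literal z_α), power 0.9 | 68.07 | 69 |
| Two-sided 0.05, power 0.8 | 62.38 | 63 |

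To get 80 from the formula, one of the inputs would have to change: a difference of about 2043 RMB, an SD of about 3902, or a power between 88% (79 per group) and 89% (81 per group). The protocol states none of these.

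**Step 2: allowance for loss.** To end with n evaluable after a loss fraction d, recruit n/(1 − d).

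| Evaluable per group | 20% loss | 25% loss |
|---|---|---|
| 80 (as stated) | 80/0.80 = 100, total 200 | 80/0.75 = 106.7, so 107, total 214 |
| 84 (as recomputed) | 84/0.80 = 105, total 210 | 84/0.75 = 112, total 224 |

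At 25%, the figure of 100 per group arises only by multiplying, 80 × 1.25 = 100, which is not the right inflation. Against the correct requirement of 84 per group (168 in total), 200 recruits tolerate a loss of 1 − 168/200 = 16%, which is below the whole planned range.

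**Step 3: power that 200 recruits give.** Power = Φ(δ/(σ√(2/n)) − 1.960).

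- 20% loss: 200 × 0.80/2 = 80 per group. Φ(3.173 − 1.960) = 88.7%; by t-test 88.4%.
- 25% loss: 200 × 0.75/2 = 75 per group. Φ(3.072 − 1.960) = 86.7%; by t-test 86.3%.
- 16% loss: 84 per group, 90.2%; by t-test 89.8%.
- No loss: 100 per group, 94.4%.

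The shortfall from 90% by the formula is therefore 1.3 points at 20% loss and 3.3 points at 25%.

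**The case against.** The strongest reply is that the slip is small and sits within the looseness of the inputs. The difference is given only as approximately 2000 RMB, and a value some 2% higher would yield 80. That is true, and it shows that four patients per group is not a large discrepancy. But no such value is printed, and it would not mend the inflation at 25%.

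The loss rate has no time point. Follow-up runs to 24 weeks, while cost and time are totalled at 12 weeks, so fewer than 20–25% may lack the primary outcome. If the loss at 12 weeks stayed at or below 16%, the formula's 90% would be reached. This stands as a possibility, but the protocol gives no separate 12-week rate and applies the 20–25% directly to the sample size for cost.

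The stated range may be loose wording: the 40 extra patients are 20% of the 200 recruited and 25% of the 160 needed. If so, the intended loss is 20% and the second error is one of description. The text does not say this, and the first error remains.

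Multiple imputation is planned in Data analysis. It would not be expected to recover much information on 12-week costs taken from patient-held diaries, and the protocol's own inflation treats lost patients as contributing nothing.

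Finally, the literal one-sided reading of z_α is not a serious alternative, because the text says the analysis is two-tailed. The request for z at alpha/2 is a matter of clear notation.

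**Conclusion.** The concern holds. On the stated inputs the requirement is 84 per group, not 80. The total of 200 matches the stated loss only at 20%, and only against the figure of 80. Across the planned loss range, power at two-sided 0.05 is 86.7% to 88.7% by the protocol's formula (86.3% to 88.4% by t-test), against 90% stated. In patients, 200 is 10 to 24 fewer than the inputs require.

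This does not threaten the viability of the trial. It is an error in the figures the trial's size rests on, and any reader can find it. The result assumes a difference of exactly 2000 RMB, an SD of 3987 in both groups, approximately normal means, losses equal in the two groups, and no information on cost from lost patients.

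All these powers are at 0.05. The Data analysis section sets an adjusted threshold of 0.002; if that applied to cost, the same formula would give about 53% with 80 per group and 49% with 75. That is a separate matter, but it is the reason to settle alpha before new figures are printed.

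**What to change.** In the Sample size section:

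1. Write the formula with the quantile for alpha/2 and correct the requirement to 84 per group. If the calculation is based on the t-test instead, the figure is 85.
2. Keep 200 recruits and restate the power at both ends of the loss range. Suggested text, at two-sided 0.05: with 200 recruited, 80 evaluable per group (20% loss) gives 88% power and 75 per group (25% loss) gives 86%, by t-test. The printed formula gives 89% and 87%. Name the method and use it for both the sample size and the power.
3. Say which time point the loss rate refers to, since cost is totalled at 12 weeks.
4. Give these figures at whichever alpha is finally adopted for cost.

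The cost is wording only, and the stated power drops by 1 to 4 points. If 90% is to be kept instead, the totals by the printed formula are 210 at 20% loss and 224 at 25%, which means enrolling 10 to 24 more patients. The Trial status section says recruitment has not begun, so either correction could be made before the first patient is enrolled.

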### Randomization and blinding

The 200 recruited patients are randomly assigned in a 1:1 ratio to either the experimental or control group using a computerized random number generator. Each patient is assigned a random number. Blinding is not possible due to the nature of the study, so neither patients nor physicians will be blinded to their group assignment. However, data analysts will not have access to any patient information other than their assigned number and will remain blinded during the statistical analysis of the collected data and presentation of results.

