**Method/design:**

This is a single-center, single-blinded, parallel randomized controlled trial conducted at Xi'an Honghui Hospital, a regional orthopedic medical center. Eligible patients will be recruited to participate in the study, and baseline data collection and clinical assessments will be conducted at the time of admission. Using the principle of random allocation, recruited patients will be divided into either the experimental or control group. Both groups will undergo a standard, widely promoted rehabilitation program. The patients in the experimental group will wear equipment to detect and track mobility in the lower limbs. All patients will return to the outpatient clinic for follow-up assessments at 2 weeks, 12 weeks, and 24 weeks after discharge, where outcome indicators will be measured. The primary outcome will be the cost and time after discharge, while secondary outcomes will include the 6-min walk test (6MWT), range of motion (ROM), visual analog scale (VAS), American Knee Society Score (KSS), the Western Ontario and McMaster Universities Osteoarthritis Index (WOMAC).

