### Interventions

During their hospitalization, both the experimental and control groups receive the same treatment regimen, rehabilitation exercise, and nursing services. After undergoing TKA, patients in the experimental group are given wearable devices and are guided to perform rehabilitation training using an APP, while patients in the control group follow a handbook for their exercise program. The rehabilitation programs for both groups are consistent and were developed in accordance with the American Academy of Orthopaedic Surgeons (AAOS) Clinical Practice Guidelines (CGPs), the American Association of Hip and Knee Surgeons (AAHKS) guidelines, and other published literature [9, 32–34]. The rehabilitation exercise program can be found in Additional file 2. Following their discharge, both groups perform the home-based exercise program for 12 weeks. The patients in the experimental group will be required to return the devices to the research team at the 12th week. Following that, both groups of patients will no longer be required to adhere to the rehabilitation program's exercise regimen.

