### Experimental group and equipment components

The patients will require assistance from the doctors to download the APP and connect the devices. The devices consist of two small monitors, which are placed about 5 cm above and below the knee joint when exercising the knee joint, and about 5 cm below the knee and the dorsum of the foot when exercising the ankle joint (refer to Fig. 2). These devices can monitor the magnitude and completion of exercises and then upload the data to the physicians' workstation. Patients can watch instructional videos on the APP to learn how to wear and exercise with the devices and then start exercising actively. The APP provides prompts for exercise frequency and whether the exercise target is reached by voice. Patients can view their exercise progress on the APP, such as the completion rate and compliance rate. Additionally, they can upload their own functional and symptomatic information to the APP, such as lower limb swelling, ecchymosis, and wound healing, in the form of videos or pictures.

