### Secondary outcomes

Secondary outcomes consist of functional performance-based tests and rating scales. The 6MWT measures the distance a patient can walk on flat ground within 6 min. To assess ROM, the patient is required to lie flat on a bed or examination table, while the examiner measures the maximum angles of flexion and extension using a standard angle measuring instrument. VAS involves the use of a 10-cm-long line with anchor points at the ends, enabling the patient to self-assess and rate the intensity of pain. The 6MWT, ROM, and VAS can effectively reflect the knee function. In addition, the KSS and WOMAC provide a comprehensive evaluation of the patient's overall condition, including knee joint function, daily living ability, and quality of life.

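### The reason given for not blinding covers patients and treating physicians, but not the examiner who measures ROM, the 6MWT and the examined part of the KSS

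*Protocol article*

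**What the plan says.** Under Randomization and blinding, the protocol article says "Blinding is not possible due to the nature of the study, so neither patients nor physicians will be blinded to their group assignment". The next sentence gives the only exception: "However, data analysts will not have access to any patient information other than their assigned number and will remain blinded during the statistical analysis". The Abstract labels the trial as single-blinded: "This is a single-center, single-blinded, parallel randomized controlled trial". On this text the label can refer only to the analysts.

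Outcomes are taken in person: "All patients will return to the outpatient clinic for follow-up assessments at 2 weeks, 12 weeks, and 24 weeks after discharge". Under Secondary outcomes, range of motion is recorded by a person: "the examiner measures the maximum angles of flexion and extension using a standard angle measuring instrument". The 6MWT is a walking performance test: "The 6MWT measures the distance a patient can walk on flat ground within 6 min". The article does not say who the examiner is, whether that person belongs to the treating team, or whether the person knows the arm.

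Two further places bear on who could learn the arm. Under Experimental group and equipment components: "The patients will require assistance from the doctors to download the APP and connect the devices". Under Interventions: "The patients in the experimental group will be required to return the devices to the research team at the 12th week". The exercise data also go to a workstation used by the physicians.

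**The concern.** The nature of the intervention makes it impossible to hide the arm from the patient or from the physician who sets up the app and follows the data. The article draws from this a general statement that blinding cannot be done, and a separate examiner at a clinic visit is then covered by a reason that does not apply to that role.

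Passive encouragement, the point at which an angle is read, and judgement in scoring can all enter a measured flexion angle, a walking distance or an examined score. If the person recording the value knows the arm, a shift in favour of the device becomes part of the data. Analyst blinding acts later and cannot remove it.

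The hypothesis at the end of the Background includes better short-term function in the experimental arm, and these measures are part of the evidence for it. The Limitations section names only the patients' reaction to being observed as a source of exaggerated differences. It does not mention the examiner.

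**Working it through.** **Does the stated reason reach the examiner?** The protocol article gives no figure to reproduce here, so the first check sets the sections side by side.

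1. *Device at the visit.* Experimental group and equipment components places the two monitors on the leg during exercise. No section has them worn at an assessment.
2. *Content of rehabilitation.* Interventions says the programmes of the two arms are consistent. The exercises themselves do not reveal the arm.
3. *Timing.* Assessments are at 2, 12 and 24 weeks. Devices go back at week 12, so none is in use at 24 weeks. Week 12 is the one time point where device return and assessment could meet.
4. *Channels by which an examiner could learn the arm.* These are helping with set-up, seeing workstation data, receiving the device, or hearing it from the patient. Visit rules can close the first three and reduce the fourth.

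Nothing in the design therefore prevents an examiner from being kept unaware of the arm.

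**Which outcomes does this touch?**

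| Outcome | Source of the value | Helped by a blinded examiner? |
|---|---|---|
| Cost, time (primary) | Patient diary | No |
| ROM | Examiner | Yes |
| 6MWT | Performance test at the visit | Yes |
| KSS | Items not listed in the article; any part scored by examination | In part |
| VAS | Patient self-rating | No |
| WOMAC | Taken here as patient-reported | No |

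**How large could the effect be?** This is an illustration only. The flexion SD and the examiner shift are assumptions and are not in the documents. The 80 per arm comes from Sample size, and the 0.002 threshold from Data analysis.

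- Assume no true difference, a constant shift *b* favouring one arm, and a two-sided normal test.
- SE = SD × √(2/80). For SD 12 this is 12 × 0.1581 = 1.90 degrees. For SD 15 it is 15 × 0.1581 = 2.37 degrees.
- P(reject) ≈ 1 − Φ(z − b/SE), with z = 1.960 at 0.05 and z = 3.090 at 0.002. The opposite tail is negligible.

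| Shift b | SD | b/SE | P(reject) at 0.05 | P(reject) at 0.002 |
|---|---|---|---|---|
| 3° | 12 | 1.58 | 0.353 | 0.066 |
| 3° | 15 | 1.26 | 0.244 | 0.034 |
| 5° | 12 | 2.64 | 0.750 | 0.325 |
| 5° | 15 | 2.11 | 0.559 | 0.163 |

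The plan's own threshold is 0.002, so the last column is the relevant one. Even its smallest entry is about 17 times the nominal level (0.034 / 0.002 = 17). A Bonferroni correction limits chance findings and does not protect against a systematic shift. No comparable figures are offered for the 6MWT or the KSS.

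**The case against.** The strongest reply is that the article never says the examiners are unblinded. The conclusion of the quoted sentence names patients and physicians only. Who examines patients, and how independent that person is, may stand in the full protocol or in the SPIRIT checklist supplied as an additional file, neither of which is shown. This stands in part: unblinded examiners are an implication, and silence in a condensed article would not by itself be a finding. But the article is not silent on blinding. It states a decision, gives a reason and lists a single exception. The reason is wrong for examiners whatever the full protocol adds.

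A reader might go further and infer that one physician sets up the app, watches the workstation, takes the device back and then measures the knee. The documents do not support that. They assign these acts to doctors, physicians, the research team and an examiner, without saying that any of them is the same person. Nor do they say that the device is handed over at the assessment visit; they give only the week.

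The reach is limited too. The primary outcomes and the sample size are unaffected, and so are VAS and WOMAC. It would be too strong to say that the whole effectiveness claim rests on examiner-measured outcomes.

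The error rates rest on assumed inputs and look much larger at 0.05 than at the plan's own threshold. They do not show that bias of this size will occur.

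Finally, an examiner can still be unblinded by a patient who mentions the device. That is a reason to call the protection partial, not a reason to omit it.

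**Conclusion.** The point holds in a limited form. The general statement that blinding is not possible is too broad: its reason fits patients and treating physicians and does not fit the examiner of ROM, the 6MWT and the examined part of the KSS. Under the rule as written, these secondary outcomes may be measured by staff who know the arm.

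No size can be derived from the documents. Under the assumptions stated (SD 12 to 15 degrees, 80 per arm, no true difference), a 3-degree examiner shift would give a significant flexion result at 0.002 in about 3% to 7% of trials, and a 5-degree shift in about 16% to 32%. The conclusion about the wording does not depend on these figures.

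The matter should be settled before the first follow-up visit. It does not threaten the primary analysis.

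**What to change.** Amend Randomization and blinding as follows.

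- Limit the statement that blinding is not possible to patients and treating physicians.
- State that the follow-up examiner of ROM, the 6MWT and the examined part of the KSS takes no part in device set-up, has no access to the workstation data, and is kept unaware of the arm at 2, 12 and 24 weeks.
- Have patients attend without the device and ask them not to disclose their arm.
- Have any device return at week 12 take place after the assessments and to another team member.
- Say what the single-blind label in the Abstract refers to.

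Add possible examiner unblinding to Limitations, and say there that the diary outcomes, VAS and WOMAC remain unblinded self-report.

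The cost is some scheduling effort and occasional accidental unblinding. An examiner is already needed at each visit, so no additional assessor is required in principle, although the article does not describe clinic staffing. Sample size, treatment and visit schedule do not change. Trial status says the trial has not begun, so on that status the rule could cover every participant.
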